## Abstract

**Background/Objectives:** Parkinson’s disease (PD) and multiple sclerosis (MS) are neurological conditions that result in debilitating non-motor symptoms, such as anxiety and depression, which significantly reduce quality of life and often persist despite pharmacological treatment. As a result, effective alternative treatment strategies are needed. Exercise therapy—particularly aerobic training—has shown promise in alleviating non-motor symptoms, potentially through neuroplastic adaptations. However, traditional aerobic exercise is often time-consuming and monotonous, limiting long-term adherence. High-intensity interval training (HIIT) offers a time-efficient and potentially more engaging alternative, though its effects on non-motor symptoms in PD and MS remain understudied. **Methods**: This transdiagnostic randomized controlled trial will enroll 48 participants (24 PD, 24 MS) with clinically significant affective symptoms (hospital anxiety and depression scale [HADS] ≥ 8). The participants will be randomly assigned to one of three 8-week interventions: (1) HIIT, 5–6 intervals of 45 s of high-intensity cycling; (2) continuous aerobic training (CAT), 50 min of low-intensity cycling; (3) movement advice (MA), step goals, and physical education. The primary (affective symptoms) and secondary outcomes (cognition, fatigue, sleep, motor function) will be assessed at four time points: 4 and 1 weeks pre intervention, and 1 and 4 weeks post intervention. Weekly blood samples and pre/post brain imaging will be collected to study biofluid and MRI measures for potential neuroplasticity. Linear mixed models will analyze the time and group effects. **Discussion:** This trial will assess whether HIIT can more effectively improve non-motor and motor symptoms in PD and MS than CAT or MA. A multimodal approach will explore both the clinical outcomes and underlying mechanisms, informing scalable and engaging rehabilitation strategies.

## 1. Introduction

Parkinson’s disease (PD) and multiple sclerosis (MS) are chronic, complex, and highly disabling neurodegenerative disorders affecting the central nervous system. PD is primarily characterized by the progressive loss of dopaminergic neurons in the substantia nigra and widespread Lewy body pathology. Increasing evidence also implicates neuroinflammation in the pathogenesis and progression of PD [1]. In parallel MS is driven by autoimmune-mediated neuroinflammation and neurodegeneration, including axonal and neuronal loss [2,3,4]. Despite these distinct pathophysiological mechanisms and clinical courses, individuals with PD and MS experience overlapping characteristics.

While motor impairments such as gait disturbances and balance difficulties are commonly recognized in PD and MS [5,6], non-motor symptoms—including anxiety, depression, cognitive deficits, fatigue, and sleep disturbances—can be equally debilitating [7,8,9,10]. Approximately 30–50% of individuals with PD or MS experience significant affective symptoms during the disease course [11,12,13], which are associated with accelerated cognitive and physical decline, reduced quality of life, and impaired overall well-being [7,14]. Although often overshadowed by motor symptoms, the profound impact of non-motor symptoms on everyday life warrants targeted interventions.

The pathophysiological pathways in both PD and MS can contribute to anxiety and depression. These neurodegenerative diseases share common mechanisms that can underlie the development of affective symptoms, including neuroinflammation, HPA axis dysregulation, neurotransmitter dysfunction, and reduced neuroplasticity, which are also related to anxiety and depression [15]. In addition, anxiety and depression in PD and MS can be exacerbated by other disease-related symptoms such as sleep disturbances, which are common, and may overlap with affective symptoms [16]. Considering these similarities, a transdiagnostic approach—focusing on the shared mechanisms and symptoms across disorders rather than disease-specific features—may offer a more holistic and efficient strategy for managing anxiety and depression in PD and MS [17,18].

While pharmacological strategies remain a cornerstone in the management of PD and MS, they often fall short in fully addressing the wide range of motor and non-motor symptoms [4,19]. Furthermore, side effects and complex drug interactions may exacerbate symptom burden [20,21,22]. As a result, there is a growing interest in alternative approaches, with exercise therapy emerging as a particularly promising intervention [23,24,25,26].

Exercise is already well established in improving motor symptoms and a growing body of evidence highlights its benefits for affective disturbances such as anxiety and depression [24,27]. Among various exercise modalities, aerobic and strength training are the most extensively studied, with aerobic training showing particular promise in alleviating affective symptoms and promoting neuroprotective mechanisms [28,29]. Traditional continuous aerobic training (CAT)—characterized by prolonged low-to-moderate-intensity exercise—has demonstrated well established and robust effectiveness on physical fitness and motor and non-motor functions but may be time-consuming and monotonous, potentially limiting adherence. Alternatively, high-intensity interval training (HIIT), involving short bursts of vigorous activity alternated with recovery periods, has emerged as a time-efficient and engaging alternative which may be superior to CAT [30,31,32,33]. In both PD and MS, HIIT has been shown to be a safe and feasible intervention, with benefits for motor symptoms, fatigue, and physical fitness [34,35,36]. Beyond these benefits, HIIT may positively influence mood [37,38]. However, the current evidence, particularly regarding its effects on non-motor symptoms such as anxiety and depression, remains limited and inconclusive [39].

Furthermore, exercise intensity appears to be an important driver of neuroplastic adaptations; however the optimal intensity remains unclear [40]. Emerging research suggests that exercise may contribute to slowing disease progression through neuroprotective mechanisms [28,29]. These include the preservation of regional brain volumes—particularly in the hippocampus and cortical areas [41,42]—the enhancement of white matter integrity (e.g., increased fractional anisotropy) [43], and the modulation of resting state functional connectivity [44]. One frequently studied mechanism is the upregulation of neurotrophic factors, such as brain-derived neurotrophic factor (BDNF), which supports synaptic plasticity, learning, and memory [45,46]. Notably, reduced BDNF concentrations have been associated with affective symptoms, including anxiety and depression [47]. Exercise, and especially high-intensity exercise, has been shown to increase BDNF expression, even in populations with neurodegenerative conditions, and this upregulation may mediate improvements in mood as well as broader neuroplastic changes [48,49,50]. This growing evidence base provides a strong rationale for evaluating exercise as a therapeutic strategy targeting both non-motor symptoms and neurobiological outcomes.

Despite the growing interest, comparative studies evaluating the effects of HIIT and CAT on non-motor symptoms and neuroplasticity in PD and MS remain scarce [51,52]. Moreover, people with these conditions may face barriers to engage in structured HIIT and CAT exercise interventions, such as limited accessibility, fatigue, or lack of time, which highlights the need for more flexible alternatives [53]. Movement advice (MA), which involves personalized guidance to increase daily physical activity, offers a pragmatic, home-based approach that may improve feasibility and adherence. We are optimistic that evaluating MA alongside CAT and HIIT will provide valuable insights into the feasibility, effectiveness, and individualization of exercise-based interventions for managing non-motor symptoms in PD and MS. This randomized controlled trial aims to investigate the effects of HIIT on non-motor symptoms, particularly anxiety and depression, compared with CAT and MA in individuals with PD and MS. Secondary objectives include evaluating the impact of exercise on blood and MRI measures of neuroplasticity, neurodegeneration, and overall quality of life.

## 2. Materials and Methods

### 2.1. Study Design and Setting

This is a single-blind, monocenter, randomized trial, with serial baseline–intervention–follow-up periods and three parallel intervention arms (see Figure 1). The total study duration per participant is 16 weeks and it will be conducted at Amsterdam UMC. All participants will perform two baseline assessments four weeks apart (i.e., baseline period), followed by an eight-week intervention period and a post intervention assessment. Subsequently, after 4 weeks a follow-up assessment will be conducted. This will allow the evaluation of baseline stability, the evaluation of the short-term durability of treatment effects, and enhanced statistical power by enabling within-subject modeling.

Eligibility criteria will be assessed during intake assessment prior to enrollment. The participants will be randomly allocated to one of the three intervention arms: (1). HIIT; (2). CAT; (3). MA. Stratified block randomization via CASTOR EDC will be used to minimize selection bias. Randomization will be stratified by disease diagnosis (PD or MS), with six blocks of four participants per diagnosis group allocated sequentially over the course of this study.

This study is approved by the medical ethical review board of the Amsterdam UMC (2021.0476). The current study status: enrollment and data collection. Additionally, blood samples will be collected and stored in the HersenFIT study biobank for future biomarker analyses, as approved by the institutional biobank review committee.

This study was prospectively registered at www.ClinicalTrials.gov (ID: NCT05357638).

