### 2.2. Participants

A total of 48 participants will be recruited: 24 individuals with PD and 24 with MS. Recruitment will occur through outpatient clinics (Departments of Rehabilitation Medicine, Neurology, and Psychiatry) at Amsterdam UMC, as well as through patient societies and social media platforms.

Inclusion criteria include (1). a clinical diagnosis of PD or progressive MS [54,55,56]; (2). for PD a Hoehn–Yahr stage of <4, indicating mild-to-moderate disability but still physically independent [57]; and for MS an expanded disability status scale (EDSS) of <6, indicating the ability to walk without assistance for at least 200 m) [58]; (3). mild affective disturbances (i.e., hospital anxiety and depression scale (HADS) ≥ 8 for the anxiety and/or depression subscale) [59,60]; (4). able to participate in intensive exercise (i.e., no contra-indications for training according to the American Colleges of Sports Medicine, including no history of heart problems or symptoms including resting electrocardiogram and no other major health issues) [61,62]; (5). sufficient cognitive abilities (Montreal Cognitive Assessment (MoCA) score > 21) [63]; (6). stable medication regimen for at least 4 weeks prior to study enrolment; (7). age ≥ 18 years; (8). able to give informed consent.

Participants are excluded in the case of (1). already participating in a high-intensity exercise program; (2). already participating in an intervention study; (3). an MS relapse 1 month prior to initiation of this study; (4). psychiatric (including suicidal ideation) or musculoskeletal disorders prohibiting participation in intensive exercise.

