#### 2.2.2. Sample Size

The sample size was calculated based on the primary outcome (HADS total score). Anticipated improvements were 6 points in the HIIT group and 3 points in the CAT group, with an standard deviation (SD) of 6 [64]. Using G*Power (version 3.1) for repeated measures analysis of variance with an alpha of 0.05 and 80% power, a total of 42 participants is required. Accounting for an expected 15% dropout rate, 48 participants will be recruited.

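### A block size of four does not fit three arms, so the randomisation as described does not secure equal allocation within diagnosis or overall

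*Protocol article*

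**What the plan says.** Section 2.1 (Study Design and Setting) has participants "randomly allocated to one of the three intervention arms": HIIT, CAT and MA. The method is given as follows: "Stratified block randomization via CASTOR EDC will be used to minimize selection bias". Diagnosis (PD or MS) is the only stratification factor, and the list is built "with six blocks of four participants per diagnosis group allocated sequentially over the course of this study".

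Section 2.2 fixes the stratum sizes: "A total of 48 participants will be recruited: 24 individuals with PD and 24 with MS".

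No allocation ratio, equal or unequal, appears anywhere in the article. Nothing says how the four places of a block are shared among the three arms. Section 2.1 also reports that the trial is already enrolling.

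**The concern.** Permuted blocks within strata are used so that the arms are balanced each time a block closes. That works when the block size is a multiple of the number of arms (or of the sum of the allocation ratio). Here three arms are paired with blocks of four. Each block must either double one arm or leave one out, and the article does not say which.

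The number of blocks and their size are stated outright, so this is not simply detail left to a fuller document: the two stated figures do not fit the stated number of arms. At stake is whether the arms end up equal within PD and within MS. Section 2.5 compares the arms with MA as the reference and examines interactions with disease, so the arm-by-diagnosis cells matter. They hold only about eight people each if allocation is equal.

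**Working it through.** **Inputs.** Three arms, two diagnosis strata, six blocks of four per stratum (section 2.1); 24 PD and 24 MS (section 2.2); SD of 6 for the HADS total (section 2.2.2).

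**The plan's own totals.** 6 × 4 = 24 per diagnosis and 2 × 24 = 48 overall, which agrees with section 2.2. Both totals divide by three (24/3 = 8, 48/3 = 16). The block size does not: 4/3 = 1.33 places per arm.

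**What six blocks of four can produce.** Assume every arm appears in every block, so each block is 2:1:1 in some order. An arm then has 6 places per diagnosis plus one for each block in which it is doubled. The article does not say how the doubled arm is chosen, so three cases are shown.

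| Rule for the extra place | Per diagnosis | Overall |
|---|---|---|
| Rotated, twice per arm in each diagnosis | 8/8/8 | 16/16/16 |
| Drawn at random in each block | from 8/8/8 to 12/6/6 | 16 per arm on average |
| Always the same arm | 12/6/6 | 24/12/12 |

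**Random extra place.** There are 3⁶ = 729 equally likely sequences per diagnosis.

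- 8/8/8 in one diagnosis: 6!/(2!·2!·2!) = 90, and 90/729 = 12.3%.
- 8/8/8 in both diagnoses: 0.123² = 1.5%.
- Largest minus smallest arm of 3 or more within a diagnosis: 10/8/6 (90), 10/7/7 (90), 9/9/6 (60), 11/7/6 (36) and 12/6/6 (3). These sum to 279, and 279/729 = 38.3%.
- 16/16/16 overall: 12!/(4!·4!·4!) = 34,650, and 34,650/3¹² = 34,650/531,441 = 6.5%.
- One arm's total is 12 + Binomial(12, 1/3): mean 16, SD √(12 × 1/3 × 2/3) = 1.63, with 2.5th and 97.5th percentiles of 13 and 19.

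The effect on precision is much smaller than these frequencies suggest. The variance of a simple two-arm contrast is proportional to 1/n₁ + 1/n₂. Averaged over all outcomes and divided by the equal-allocation value, it is 1.011 overall (against 2/16) and 1.021 within a diagnosis (against 2/8). That is a loss of about 1% and 2%.

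**Same arm always doubled (24/12/12).**

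- Smaller arm against smaller arm: (1/12 + 1/12)/(1/16 + 1/16) = 0.1667/0.125 = 1.33. With SD 6 the standard error is 6 × √0.1667 = 2.45, against 6 × √0.125 = 2.12, about 15% larger.
- Doubled arm against either smaller arm: 1/24 + 1/12 = 0.125 = 2/16. The standard error stays at 2.12, so nothing is lost.
- If MA, the reference group in section 2.5, were the doubled arm, both contrasts against it would keep full precision and only HIIT versus CAT would lose.

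**Block sizes that fit.** Multiples of three that divide 24 are 3 (eight blocks), 6 (four blocks) and 12 (two blocks). Each gives 8/8/8 per diagnosis and 16/16/16 overall when the blocks are filled. Four blocks of six also makes 24, so the published phrase may be a transposition of it. The article cannot confirm that.

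**The case against.** A reader might infer that blocks of four make equal allocation impossible. The documents do not support that. Both 24 and 48 divide by three, and rotating the doubled arm gives exact equality within each diagnosis and overall. Even with a random extra place, 8/8/8 arises about one time in eight. What the scheme lacks is a guarantee.

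A reader might also infer that the randomisation actually in use is faulty. The article shows only a sentence that does not fit the design. The list in the EDC may be sound and the wording transposed. Nor is 1:1:1 stated: it is a reasonable inference from the absence of any unequal ratio and from totals that divide by three, but it remains an inference.

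The harm is easily overstated. A random extra place costs 1–2% in variance, and a fixed 2:1:1 list weakens one contrast of three. Unequal arm sizes do not in themselves bias the mixed model of section 2.5, and the sample sizes of 42 and 48 are unaffected.

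Predictability is a weak supplementary argument. If the doubled arm varies, the last place of a block is fully determined in 6 of the 12 possible orderings; with a known fixed 2:1:1 composition it always is. But the last place of a fixed block of three is always determined too, so this weakness belongs to any fixed, known block size. Advice to withhold the block size is moot now that it is published.

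All of this limits the consequence. It does not remove the mismatch: a stated block size that does not fit the stated number of arms, with no ratio or rule to explain it.

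**Conclusion.** The point holds in limited form. As described, no block can be balanced 1:1:1, and the scheme does not secure 8/8/8 per diagnosis or 16/16/16 overall, although it does not preclude them. The cost depends on how the fourth place is filled: none if it rotates, about 1–2% in average contrast variance if it is random, and a 33% rise in variance for the contrast between the two smaller arms if one arm is always doubled.

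This rests on two assumptions: that equal allocation is intended, and that every arm appears in every block. If an unequal ratio is intended, the defect is that neither the ratio nor the doubled arm is stated. Severity is moderate: the description needs correcting or explaining while enrolment is open, but neither the validity of the primary estimate nor the planned sample size turns on it.

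**What to change.** 1. Have someone independent of recruitment and assessment check the list held in the EDC: the block sizes, the composition of each block and the ratio.
2. If the list is sound and the text is wrong (for instance, four blocks of six was meant), correct the text and state the allocation ratio.
3. If the list really uses blocks of four and equal allocation is intended, leave past allocations as they are. Generate the unused part with block sizes that are multiples of three, such as blocks of six or a concealed mix of threes and sixes, and state 1:1:1.
4. If an unequal ratio is intended, state it, name the doubled arm and give the reason.

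The cost is a check of the list and a protocol note, plus a new list for the remaining participants only if blocks of four prove to be in use. The sample size does not change. The list can be changed only while enrolment is open; afterwards any imbalance is permanent.

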### 2.2. Participants

A total of 48 participants will be recruited: 24 individuals with PD and 24 with MS. Recruitment will occur through outpatient clinics (Departments of Rehabilitation Medicine, Neurology, and Psychiatry) at Amsterdam UMC, as well as through patient societies and social media platforms.

Inclusion criteria include (1). a clinical diagnosis of PD or progressive MS [54,55,56]; (2). for PD a Hoehn–Yahr stage of <4, indicating mild-to-moderate disability but still physically independent [57]; and for MS an expanded disability status scale (EDSS) of <6, indicating the ability to walk without assistance for at least 200 m) [58]; (3). mild affective disturbances (i.e., hospital anxiety and depression scale (HADS) ≥ 8 for the anxiety and/or depression subscale) [59,60]; (4). able to participate in intensive exercise (i.e., no contra-indications for training according to the American Colleges of Sports Medicine, including no history of heart problems or symptoms including resting electrocardiogram and no other major health issues) [61,62]; (5). sufficient cognitive abilities (Montreal Cognitive Assessment (MoCA) score > 21) [63]; (6). stable medication regimen for at least 4 weeks prior to study enrolment; (7). age ≥ 18 years; (8). able to give informed consent.

Participants are excluded in the case of (1). already participating in a high-intensity exercise program; (2). already participating in an intervention study; (3). an MS relapse 1 month prior to initiation of this study; (4). psychiatric (including suicidal ideation) or musculoskeletal disorders prohibiting participation in intensive exercise.

#### 2.2.1. Safety Monitoring and Withdrawal

Safety procedures will follow the protocol approved by the accredited medical ethical review board. All adverse events are recorded and graded according to the Common Terminology Criteria for Adverse Events. Serious adverse events will be reported within 7 days to the accredited medical ethical review board.

All exercise sessions will be supervised by qualified physiotherapists experienced in managing Parkinson’s disease and multiple sclerosis, ensuring the appropriate handling of disease-specific risks during training.

Participation is voluntary. The participants may withdraw at any time. Those who withdraw before completing the second baseline assessment will be replaced; those who withdraw from the intervention phase will be invited to complete the post intervention and follow-up assessments.

#### 2.2.2. Sample Size

The sample size was calculated based on the primary outcome (HADS total score). Anticipated improvements were 6 points in the HIIT group and 3 points in the CAT group, with an standard deviation (SD) of 6 [64]. Using G*Power (version 3.1) for repeated measures analysis of variance with an alpha of 0.05 and 80% power, a total of 42 participants is required. Accounting for an expected 15% dropout rate, 48 participants will be recruited.

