### 2.3. Outcome Assessment

Baseline assessments will include demographic, disease-specific characteristics, and pharmacotherapy (participants will be asked to maintain their existing regimen unless medically required to adjust). The assessor will be blinded to group allocation. Outcome measures will be assessed at baseline, pre intervention (week 4), post intervention (week 12), and follow-up (week 16). An overview is provided in Table 1.

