### 2.5. Statistical Analysis

Statistical analyses will be conducted using R or Stata, with the significance set at *p* < 0.05 (two-tailed). The primary analysis will follow the intention-to-treat principle and per protocol analysis will be performed as a sensitivity analysis.

Continuous variables will be presented as mean (SD) or median [IQR] values based on normality. Categorical variables will be reported as frequency (%). Normality will be assessed using histograms and Q-Q plots. In case normality assumptions are violated, a log-transformation will be explored.

Baseline characteristics, including age, sex, disease severity, anxiety, depression, and medication use, will be presented for each intervention arm and for each disease type (PD, MS) using descriptive statistics.

Linear mixed models (LMMs) will be used to analyze the longitudinal changes in anxiety and depression across time points (baseline, intervention, and follow-up) and between intervention arms (HIIT, CAT, and MA). These factors will be added to the model as fixed factors. All outcomes will serve as dependent variables in separate models. Participant ID will be added to the model as a random effect to account for intra-individual correlations. Age, sex, medication, and mobility severity (i.e., TUG) will be added to the model as covariates and interaction effects for disease will be investigated. Exploratory subgroup analyses will be conducted if the interaction term is significant. The MA group will be the reference group.

The analyses of secondary outcomes will be exploratory in nature. No formal adjustment for multiple comparisons will be applied; exact *p*-values will be reported, and the results will be interpreted cautiously considering the increased risk of Type I error.

For all primary and secondary outcomes, estimated effects with 95% confidence intervals will be reported from the LMM, alongside standardized effect sizes (Hedges’ g with 95% confidence interval) to facilitate clinical interpretation.

Missing data will be expected, but LMMs are generally robust to missing data. Outliers will be identified using residual diagnostics and sensitivity analyses will be performed with and without outliers to evaluate robustness.

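### The 80% power stated for 42 participants does not apply to the only effect given, the 3-point HIIT–CAT difference, under ordinary assumptions

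*Protocol article*

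**What the plan says.** Section 2.2.2 sizes the trial on HADS total: "The sample size was calculated based on the primary outcome (HADS total score"). The effect is given as: "Anticipated improvements were 6 points in the HIIT group and 3 points in the CAT group, with an standard deviation (SD) of 6". The method and result follow: "Using G*Power (version 3.1) for repeated measures analysis of variance with an alpha of 0.05 and 80% power, a total of 42 participants is required". Recruitment is then set: "Accounting for an expected 15% dropout rate, 48 participants will be recruited".

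The section does not give the effect size f, the type of repeated-measures test, the number of groups or measurements, the correlation, or an improvement for MA. It also does not say whether 6 is the SD of a score or of a change.

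Elsewhere the article fixes three arms (Section 2.1: "The participants will be randomly allocated to one of the three intervention arms: (1). HIIT; (2). CAT; (3). MA") and four HADS assessments (Section 2.3: "Outcome measures will be assessed at baseline, pre intervention (week 4), post intervention (week 12), and follow-up (week 16"). Testing is two-sided (Section 2.5: "with the significance set at *p* < 0.05 (two-tailed"). The Introduction states the aim as comparing HIIT with CAT and with MA.

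**The concern.** A reader will take the 80% as power to detect the one difference that the section names, HIIT 3 points better than CAT. That difference is half an SD. With three arms, 42 participants leave 14 per arm, and half an SD normally needs far more than that.

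If the 80% belongs to some other test, the article credits the HIIT–CAT comparison with a sensitivity it lacks. In most of the scenarios below, a non-significant HIIT–CAT result would then be about as likely as a significant one, or likelier, even if the assumed benefit were real.

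**Working it through.** **Inputs.** From Section 2.2.2: difference 6 − 3 = 3, SD 6, alpha 0.05, power 80%, N = 42, dropout 15%, 48 recruited. From Sections 2.1, 2.3 and 2.5: three arms, two HADS visits before and two after the intervention, two-sided testing. Assumed here: equal arms (42/3 = 14) and an equal correlation rho between any two visits. Where rho is used, 6 is taken as the SD of a score at one visit.

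**1. Reproducing 42.** For a within-between interaction with k groups and m measurements, lambda = f²·N·m/(1 − rho), df1 = (k − 1)(m − 1) and df2 = (N − k)(m − 1). Take f = d/2 = (3/6)/2 = 0.25, k = 3, m = 2, rho = 0.5.

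- N = 42: lambda = 0.0625 × 42 × 2/0.5 = 10.5, df 2 and 39, power 0.803.
- N = 41: power 0.792.

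So 42 is matched exactly, with f, k, m and rho inferred.

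**2. What f the stated difference implies.** In this test, f is the root mean square of the cell interaction effects divided by the SD. Changes of 6 and 3 deviate from their mean by ±1.5. Split over two time points this is ±0.75, so f = 0.75/6 = 0.125, half the value used above. With two groups and rho 0.5, N = 128 gives lambda = 0.015625 × 128 × 2/0.5 = 8.0 and power 0.80. That is 64 per arm, the same as an ordinary two-sample comparison at d = 0.5.

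**3. Three-arm interaction at N = 42, m = 2.** This needs an MA improvement, so a range is shown.

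| MA improvement | f | Power, rho 0.5 | rho needed for 80% |
|---|---|---|---|
| 0 | 0.204 | 62% | about 0.67 |
| 1.5 | 0.156 | 40% | about 0.80 |
| 3 | 0.118 | 24% | about 0.89 |

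Example for MA = 0: deviations 3, 0, −3, halved to 1.5, 0, −1.5; root mean square √(4.5/3) = 1.225; f = 1.225/6 = 0.204; lambda = 0.0417 × 42 × 4 = 7.0.

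**4. HIIT versus CAT, 14 per arm.** Noncentral t with 26 df and noncentrality 3/(SD·√(2/14)). For the mean of b post visits adjusted for the mean of a pre visits, SD² = 36·[(1 + (b − 1)rho)/b − rho²·a/(1 + (a − 1)rho)].

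| Analysis | rho | SD | Power | Difference detectable at 80% |
|---|---|---|---|---|
| Unadjusted post value, or change at rho 0.5 | – | 6.00 | 25% | 6.6 |
| One post, adjusted for two pre | 0.5 | 4.90 | 35% | 5.4 |
| One post, adjusted for two pre | 0.7 | 3.90 | 50% | 4.3 |
| Two posts averaged, adjusted for two pre | 0.5 | 3.87 | 51% | 4.3 |
| Two posts averaged, adjusted for two pre | 0.7 | 3.14 | 68% | 3.5 |
| Two posts averaged, adjusted for two pre | 0.8 | 2.61 | 83% | 2.9 |

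For the first row the noncentrality is 3/(6 × 0.378) = 1.32 against a critical value of 2.06. If all 48 are retained (16 per arm), that row rises to 28%. Averaging both post visits assumes that the full 3-point difference persists to follow-up.

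**5. Dropout.** 42/0.85 = 49.4, so 50. Conversely, 48 × 0.85 = 40.8.

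**The case against.** **42 is not an arithmetic slip.** A reader might infer that it cannot be derived at all. The documents do not support that: a standard set-up reproduces it exactly, and the full protocol may hold the inputs that a condensed article omits. This objection stands. The fault lies in how the effect is scaled and which comparison the 80% covers.

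**f = 0.25 does not prove that a 6-point HIIT–CAT difference was assumed.** That equivalence holds only for two groups. With three groups f depends on MA: changes of 6, 3 and −1.3 also give f = 0.25 with HIIT and CAT still 3 apart. This stands too, although it requires MA to worsen, while Section 3 expects all three interventions to improve symptoms.

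**The omnibus test can reach 80%.** With MA at 0 it does so at rho about 0.67. With four measurements and an effect equal at both post visits, it has 79% at rho 0.5. Section 2.2.2 also attaches the 80% to a repeated-measures analysis of variance rather than explicitly to HIIT versus CAT. All this is true, but no MA value is stated, and any MA improvement lowers these figures.

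**Power need not be as low as 25–50%.** The planned mixed model uses all four visits, and Section 2.1 claims extra power from the serial design. The favourable rows therefore belong in the range. They still fall short of 80% at rho 0.5–0.7.

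**Dropout and interpretation are largely covered.** Multiplying 42 by 1.15 gives 48.3, early withdrawals are replaced, and the mixed model uses partial data. Section 2.5 already promises 95% confidence intervals and Hedges' g. Nothing in the article says that a non-significant result will be read as equivalence; that is a risk, not a stated plan.

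**Conclusion.** The concern holds for the contrast, not for the arithmetic of 42. The only effect stated is 3 points between HIIT and CAT with SD 6, and 14 per arm does not give it 80% power under ordinary assumptions. Power is about 25% unadjusted, 35–50% with one adjusted post visit, and 51–68% with both post visits averaged and the effect maintained (rho 0.5–0.7). It passes 80% in that last case only at rho about 0.8. The three-arm test does not settle the matter, because its power rests on an unstated MA improvement: 62% at 0 points and 24% at 3 (two measurements, rho 0.5).

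These figures assume equal arms and equal correlations between visits. The inputs used to match 42 are inferred, so half the standardised difference is only the likely source of f = 0.25. The dropout shortfall is about one participant and is minor.

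**What to change.** Keep N = 48 and rewrite the justification in Section 2.2.2:

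- State the test or contrast to which the 80% refers, and the number of measurements, correlation and MA improvement behind it.
- For HIIT versus CAT, replace the 80% with the power under those stated assumptions, or give the detectable difference: about 6.6 points unadjusted, 4.3–5.4 with one adjusted post visit, or 3.5–4.3 with both post visits averaged (rho 0.7–0.5).
- Note that 48 less 15% leaves about 41, just under 42.
- Say that HIIT versus CAT will be read from its 95% confidence interval and that non-significance is not evidence of equivalence.

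The cost is text only. No participants are added and no procedure changes, but the stated power becomes less favourable. Enrolment is under way, so the change is best made before results are known.
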